#### Aim 4: Explore Intervention Translatability

The implementation and dissemination of the adapted Family Gene Toolkit will be evaluated based on the constructs of the RE-AIM framework [51] at the individual and organizational levels.

### Settings

The DIALOGUE study involves oncology and genetic testing centers of the Swiss CASCADE Consortium from 3 linguistic regions of Switzerland (German-, French-, and Italian-speaking) and similar settings in Korea, eg, Severance Hospital, Seoul, and the National Cancer Center, Goyang. Settings ensure diversity in hospital characteristics (eg, general or advanced level) and geographic location to increase sample representativeness and generalizability.

### Sample and Sample Size

The DIALOGUE study targets individuals who have been identified through genetic testing as carrying a *BRCA* pathogenic variant (proband) and their blood relatives. Textbox 1 describes the inclusion criteria for the probands and relatives. Eligible probands will be females and males (expected female-to-male ratio=4:1) and their first- and second-degree relatives (parents, siblings, offspring, aunts, uncles, nieces, nephews, and grandparents) and their first cousins. Participants may have a cancer diagnosis (expected breast-to-ovarian cancer ratio=5:1) or they may be cancer-free. Individuals who tested positive for a variant of uncertain significance and mutation carriers without any blood relatives, spouses, and partners are excluded because cascade genetic testing does not apply to them. We also exclude individuals who tested positive for a non-*BRCA* pathogenic variant because of the current variation in the implementation of panel testing among the different sites, which will likely influence the recruitment of participants with non-*BRCA* mutations. The study will only include adults because hereditary cancer risk assessment is not recommended for children. The study will also exclude vulnerable participants, such as critically ill patients and those living in nursing homes, to avoid increasing the subject burden and provide surveillance recommendations to participants who are not able to follow through the program.

Inclusion criteria.SwitzerlandProbandsHas tested positive for a BRCA pathogenic variant≥1 first- or second-degree relative or first cousinProbands and relatives≥18 years oldGerman, French, Italian, and EnglishSwiss residentMentally able to provide written consentAccess to computer, tablet, or smartphoneKoreaProbandsHas tested positive for a BRCA pathogenic variant≥1 first- or second-degree relative or first cousinProbands and relatives≥19 years oldKorean and EnglishKorean residentMentally able to provide written consentAccess to computer, tablet, or smartphone

#### K-CASCADE Cohort

Estimates of sample accessibility follow consultations with the medical directors of clinical sites and assume average HBOC prevalence rates of 5% for both countries. There are approximately 90 new mutation carriers per year from the clinical centers affiliated with the Swiss CASCADE Consortium. Data from the Swiss CASCADE cohort indicate that it is feasible to recruit approximately 50% of the probands from each clinical site. Each proband is willing to invite an average of 4 relatives, with a response rate of 50% among relatives. In Korea, with 5 participating hospitals, 540 individuals are expected to enter the K-CASCADE cohort over 3 years (6 individuals per month×12 months×3 years×5 hospitals, 50% participation rate).

#### Intervention Adaptation

A purposeful sample of 20-24 participants (10-12 mutation carriers and 10-12 relatives) per linguistic region will participate in individual interviews and/or mini focus groups in each country. There will be homogeneity within members of each focus group, but the samples will be diversified in terms of demographics (eg, sex) and clinical history (eg, affected with cancer vs cancer-free) among groups. Mini focus groups or interviews will be conducted with a convenience sample of 6-10 expert clinicians involved in genetic consultation in each country. Mini focus groups allow more time to share experiences and encourage greater in-depth information and insights. The adapted Family Gene Toolkit will be tested for usability and acceptability with 5 new mutation carriers and/or relatives per linguistic region [52,53].

#### Intervention Efficacy

The cluster RCT will invite 114 probands to have a total of 104 evaluable subjects (52 for each website). This sample size would allow detecting whether using the adapted Family Gene Toolkit or the comparison website would increase the proportion of informed relatives by 25% with a statistical power of 80%, a significance level of 5%, and a dropout rate of 9.6% (11/114). We estimated the distribution of the proportion of relatives and dropout rates from our previous studies [14,50]. Less than 10.5% (12/114) of potential participants have no relatives, and less than 10.5% (12/114) have no access to a computer, tablet, or smartphone, making them ineligible for the study. We expect to recruit and retain the final sample of 114 probands over 18 months.

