**Methods:**

The digital health intervention will be available in French, German, Italian, Korean, and English and can be accessed via the web, mobile phone, or tablet (ie, device-agnostic). K-CASCADE cohort of Korean HBOC mutation carriers and relatives will be based on the CASCADE infrastructure. Narrative data collected through individual interviews or mini focus groups from 20 to 24 HBOC family members per linguistic region and 6-10 health care providers involved in genetic services will identify the local cultures and context, and inform the content of the tailored messages. The efficacy of the digital health intervention against a comparison website will be assessed in a randomized trial with 104 HBOC mutation carriers (52 in each study arm). The translatability of the digital health intervention will be assessed using survey data collected from HBOC families and health care providers.

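### The sample-size figures contradict each other: 11 dropouts from 114 leave 103 evaluable probands, not 104, and 114 is labelled in ways that cannot all be true (minor; no power shortfall shown)

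*Protocol article*

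**What the plan says.** Four statements in the protocol article's Intervention Efficacy paragraph, under Sample and Sample Size, and one in the abstract bear on the trial's size.

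- Number invited and number evaluable: "The cluster RCT will invite 114 probands to have a total of 104 evaluable subjects (52 for each website".
- Dropout, given alongside 80% power, a 5% significance level and a 25% increase in the proportion of informed relatives: "a dropout rate of 9.6% (11/114".
- Ineligibility among potential participants, for two reasons: "Less than 10.5% (12/114) of potential participants have no relatives, and less than 10.5% (12/114) have no access" to a suitable device.
- Recruitment: "We expect to recruit and retain the final sample of 114 probands over 18 months".
- Abstract, Methods: a "randomized trial with 104 HBOC mutation carriers (52 in each study arm".

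Allocation is 1:1 (Recruitment and Procedures). The primary comparison is a two-sided Wilcoxon-Mann-Whitney test (Data Management and Data Analyses). The assumed distribution of the per-family proportion comes from earlier studies and is not shown.

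**The concern.** Read together, these statements do not give one set of numbers. The printed dropout applied to 114 does not produce the printed evaluable total. The figure 114 also has four roles: people invited, denominator for dropout, denominator for ineligible potential participants, and final sample recruited and retained. If 114 are retained, 11 have not dropped out. If 11 drop out, 114 are not retained. The abstract's randomised total of 104 is the paragraph's evaluable total.

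The sample size is the figure against which recruitment is run and later reported. A reader should be able to tell which number is approached, which is randomised and which is expected in the analysis. Here a site or a later reader could take 114 as any of the three.

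**Working it through.** **Inputs.** From the protocol article: 114 probands, 104 evaluable (52 per arm), dropout 9.6% printed as 11/114, two ineligibility rates each below 10.5% printed as 12/114, 80% power, two-sided 5% level, 1:1 allocation.

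**1. The plan's own figure, forwards.**
- 11/114 = 9.65%, in line with the printed 9.6%.
- 114 − 11 = 103, and 114 × (1 − 0.096) = 103.06. The plan states 104.
- For 104 to remain, losses must be 114 − 104 = 10, and 10/114 = 8.77%.

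**2. The plan's own figure, backwards.**
- Correct inflation: 104/(1 − 0.096) = 115.04, which rounds up to 116 for equal arms.
- Multiplying instead: 104 × 1.096 = 113.98, or 114. Also 10/104 = 9.62%.
- So 114 and 9.6% fit together if the rate was taken on 104 and applied as a multiplier. The printed fraction 11/114 uses a different denominator. This origin is an inference; the protocol does not show its formula.

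**3. Power at 103 evaluable.** The 80% cannot be rebuilt independently, because neither the control value nor the spread of the proportion is given. It can be held fixed at 52 per arm and scaled. Under the normal approximation with n per arm,

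power(n) = Φ(2.802 × √(n/52) − 1.960),

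where 2.802 = 1.960 + 0.842 is the value that gives 80% at n = 52. If the 25% is an absolute difference of 0.25, this implies an SD of 0.455 (0.445 or 0.423 with Wilcoxon efficiencies of 0.955 or 0.864). The scaled power is the same for each of these.

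- n = 51.5 (103 in total): Φ(2.788 − 1.960) = 79.6%.
- Difference from 80.0%: 0.4 percentage points.

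**4. The most literal reading of the invitation sentence.** Suppose 114 were only approached, and nobody else were recruited.

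| Ineligibility assumed | Eligible | Evaluable at 11/114 dropout | Power |
|---|---|---|---|
| Both bounds in full, no overlap (12 + 12) | 90 | 90 × 103/114 = 81.3 | about 70% |
| Both bounds in full, complete overlap (12) | 102 | 102 × 103/114 = 92.2 | about 75% |

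These rows show what the wording could mean at its worst. The protocol does not state them as expectations.

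**The case against.** The strongest reply is that this is loose wording around a sound calculation. The number 114 is 104 raised by 9.6%, and 9.6% of 114 is 10.94, which rounds to the printed 11. The discrepancy is one proband, within the tolerance one would allow for rounding. Power is stated for 104 evaluable, and the abstract's 104 matches that total in condensed form. All of this stands as to size. It does not make 114 − 11 equal 104, and it does not reconcile a retained sample of 114 with 11 dropouts.

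A reader might go further and infer that 24 of the 114 are expected to be ineligible, that participation would halve the rest, and that the 80% power is therefore missed by a wide margin. The document does not support this, for four reasons.

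- The two ineligibility rates are upper bounds on potential participants. They may overlap, and the protocol never adds them.
- Eligibility is settled before trial entry. The inclusion criteria require a relative and a device. For the cohort, carriers meet recruiters and consent only if they have an eligible relative by pedigree. Trial access follows the baseline survey and agreement to take part.
- The statement that "it is feasible to recruit approximately 50% of the probands from each clinical site" stands under the K-CASCADE Cohort heading and describes entry to the cohort, not uptake of the trial among those already enrolled.
- Nothing says that recruitment stops at 114 invitations. The paragraph's last sentence speaks of recruiting 114.

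**Conclusion.** The concern holds as a reporting inconsistency of minor severity. As printed, the figures cannot all be right: 11 dropouts from 114 give 103, and 114 cannot be both retained in full and reduced to 104 evaluable. The abstract labels the evaluable number as the trial size.

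The demonstrated consequence is one proband and about 0.4 points of power, 79.6% against 80%. This rests on holding fixed the effect that gives 80% at 52 per arm, and on a normal approximation. If 114 are randomised after screening, power is about 80% as stated. It would fall to about 70% only if three things were all true: 114 is the number approached, both ineligibility bounds apply in full without overlap, and nobody else is recruited. The document states none of them, so no power shortfall has been shown.

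**What to change.** Rewrite the paragraph so that each number has one label.

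- State that 114 probands (57 per arm) will be randomised after eligibility screening.
- Then choose one of two corrections. Either keep the 9.6% dropout (11/114) and give 103 expected evaluable, with power of about 79.6%; or keep 104 evaluable and correct the dropout to 10/114 (8.8%), if the earlier studies support that rate.
- Replace the wording that 114 are invited, and the wording that a final sample of 114 is retained.
- Report the two ineligibility rates as bounds that apply before randomisation, without 114 as their denominator.
- In the abstract, say that 104 is the number expected to be evaluable (or 103, if the first correction is chosen).

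The cost is a few sentences. Neither correction needs extra participants or a change of design. If the sponsor would rather keep both 104 evaluable and 9.6% dropout, about 116 must be randomised, which is two more than planned.

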#### Intervention Translatability

This step involves assessing the potential for implementing the adapted Family Gene Toolkit in real-world conditions. RE-AIM dimensions will be assessed from participating and nonparticipating mutation carriers, relatives, and providers throughout the study.

### Recruitment and Procedures

#### K-CASCADE Cohort

The opportunity to participate in the K-CASCADE cohort will be advertised through the KOHBRA network, the Ovarian Cancer and Genetics study group, and other clinical sites. Recruitment procedures for Korean probands and relatives will follow steps and procedures similar to those outlined for the Swiss CASCADE cohort [14]. In short, index cases (first person in the family with the pathogenic variant) identified in participating centers will be invited to participate in the study by collaborating clinicians and through patient advertisements posted in the clinics. Potential participants will also be able to view information on the study website. Individuals carrying a *BRCA* pathogenic variant, and if they have at least one eligible relative based on pedigree data, will meet study recruiters to ask questions and provide written consent. To alleviate ethical concerns associated with contacting blood relatives without their explicit consent, the K-CASCADE cohort will approach them through probands, targeting only relatives the proband is willing to contact. This recruitment method is used by the Swiss CASCADE cohort and in previous family-based studies with very good recruitment outcomes [39,54]. Relatives agreeing to participate will also provide written consent. In the consent form, probands and relatives will indicate their willingness to invite additional relatives to the K-CASCADE, be contacted once a year for 5 years and provide updated information about their health, participate in a focus group or individual interview for the adaptation of the Family Gene Toolkit in Korean, and participate in an RCT for testing the effects of the adapted Family Gene Toolkit. Probands and relatives may participate in all or some of the study steps previously described.

Probands and relatives will provide baseline assessments via a URL link to the digital health intervention and a unique passcode. A second prompt will be sent 2 weeks later. If there is no response to the second contact, study recruiters will contact the participants by phone. Relatives will also provide written consent, and they will receive a URL with a unique passcode. The Swiss CASCADE platform will facilitate data collection in both countries to maintain the consistency and accuracy of data entry, data management, and analyses. Korean respondents will log on as K-CASCADE participants to provide survey data.

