#### Intervention Adaptation

Participants will be recruited through the Swiss CASCADE cohort and through flyers posted in the affiliated Korean institutions and clinics. After obtaining consent, focus groups or individual interviews will be organized at an easily accessible site and in participants’ language. Focus groups will be coded by 2 members of the team in each country and linguistic region and will be audiotaped with participants’ explicit consent. Participants will be asked to *think aloud* while viewing electronic mockups of the intervention and while navigating a final version of the digital health intervention. The latter sessions will be videotaped.

Clinicians involved in genetic consultations will be identified through the CASCADE Consortium in Switzerland; through the Schweizerischen Arbeitsgemeinschaft für Klinische Krebsforschung, Network for Cancer Predisposition Testing and Counseling in Switzerland; and through the KOHBRA network in Korea. They will be recruited via email and/or invitation letters and will also provide consent. Semistructured exploratory questions will elicit their opinions on structural barriers to HBOC cascade genetic testing. At a later stage, they will also view a nearly final version of the digital health intervention and will provide feedback. Sessions will be audiotaped and videotaped with clinicians’ consent.

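### People shown the intervention in adaptation or usability sessions are not kept out of the RCT, so pre-exposed families can enter either arm and dilute the primary contrast

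*Protocol article*

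**What the plan says.** Under Recruitment and Procedures, K-CASCADE Cohort, the consent form asks probands and relatives whether they are willing to "participate in a focus group or individual interview for the adaptation of the Family Gene Toolkit in Korean, and participate in an RCT". The paragraph closes by saying that "Probands and relatives may participate in all or some of the study steps previously described".

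Under Recruitment and Procedures, Intervention Adaptation, the source of the adaptation sample is given: "Participants will be recruited through the Swiss CASCADE cohort and through flyers posted in the affiliated Korean institutions and clinics". Participants think aloud "while viewing electronic mockups of the intervention and while navigating a final version of the digital health intervention".

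Under Sample and Sample Size, Intervention Adaptation, the size is "A purposeful sample of 20-24 participants (10-12 mutation carriers and 10-12 relatives) per linguistic region". The adapted toolkit is then "tested for usability and acceptability with 5 new mutation carriers and/or relatives per linguistic region".

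The exclusions under Sample and Sample Size, and the inclusion criteria in Textbox 1, do not mention earlier contact with the intervention. Aim 3 and the Intervention Efficacy procedures randomise 1:1 by family after baseline, stratified by country only. The analysis section names an unadjusted Wilcoxon-Mann-Whitney test for the proportion of informed relatives.

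**The concern.** The adaptation work produces the intervention that the RCT tests, so anyone who does both meets the content before being randomised. That person may then be allocated to the comparison website having already handled the active product, or to the intervention having already taken in part of it. In both cases the family contributes less to the arm difference than the design assumes.

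The primary outcome makes this more than a formality. A relative who has been informed stays informed, so a proband prompted to disclose by a session has less left to gain in either arm. The interview guide itself covers decisions about disclosing results to relatives. Relatives also attend sessions and follow the proband's allocation, so exposure works through the family, and a count of exposed carriers alone may understate it. The stated design has 80% power and no declared margin above that.

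**Working it through.** **1. Is overlap permitted, and where?**
- Korea: yes, expressly. One consent form lists both steps, and the closing sentence allows all of them.
- Switzerland: not expressly. The point rests on recruitment of the adaptation sample from the Swiss CASCADE cohort and on the absence of any exclusion.
- The word new in the usability sentence separates those testers from the earlier session participants. It does not separate them from the RCT.

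**2. How many people could overlap?** (Sample and Sample Size; Settings)
- Explicit Korean permission: 10 to 12 carriers. 10/114 = 8.8% and 12/114 = 10.5%, so about 9-11% of the probands to be invited. At most 5 Korean usability testers come on top.
- Ceiling over four linguistic regions (German, French, Italian, Korean): 4 × 10 = 40 to 4 × 12 = 48 carriers. 40/114 = 35% and 48/114 = 42%. Usability testing adds 4 × 5 = 20 people, who may be carriers or relatives.
- These are upper limits on possible overlap. The article gives no expected overlap.

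**3. The plan's own sample size.** Stated: 114 invited, 104 evaluable, 52 per arm, a 25% increase (read here as 25 percentage points), 80% power, two-sided 5%, 9.6% dropout.
- Dropout: 104 / (1 − 0.096) = 115.04, close to 114.
- The 52 per arm cannot be fully reproduced, because no control proportion or standard deviation (SD) is given. It is consistent with a comparison of means: n per arm = 2 × (1.96 + 0.84)² × SD² / 0.25² gives 52 at SD = 0.455.
- The point does not depend on the sample size being wrong.

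**4. Dilution.** Let f be the share of the 104 evaluable probands who are pre-exposed, equal in both arms in expectation. Let c be the share of the intervention effect that exposure has already delivered. Both are assumptions.
- Diluted difference = 25 × (1 − f × c) points.
- Power = Φ[2.80 × (1 − f × c) − 1.96], where 2.80 = 1.96 + 0.84 is the value implied by 80% power. The result does not depend on the SD.

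| Pre-exposed probands of 104 | f | Half carry-over (c = 0.5) | Full carry-over (c = 1) |
|---|---|---|---|
| 0 | 0 | 25 points, 80% | 25 points, 80% |
| 5 | 4.8% | 24.4 points, 78% | 23.8 points, 76% |
| 10 | 9.6% | 23.8 points, 76% | 22.6 points, 72% |
| 20 | 19.2% | 22.6 points, 72% | 20.2 points, 62% |
| 40 (near the ceiling) | 38.5% | 20.2 points, 62% | 15.4 points, 41% |

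Worked example, 10 probands with full carry-over: 1 − 0.096 = 0.904; 2.80 × 0.904 = 2.53; 2.53 − 1.96 = 0.57; Φ(0.57) = 0.72.

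**The case against.** The permissive sentence is consent language in the Korean section, and the adaptation it refers to is the Korean one. Swiss cohort procedures are in a cited protocol that is not shown. The eligibility text serves the whole DIALOGUE study, so a rule specific to the RCT might sit in the full protocol. This limits the explicit permission to Korea, and that limit stands. It does not remove the point: an exclusion elsewhere would contradict the printed sentence for Korea, and nothing printed protects the Swiss part.

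A reader might infer that 35-42% of probands will be pre-exposed and that power will fall to about 40%. The documents do not support that. It would require every adaptation carrier in all four regions to become an RCT proband, with full carry-over. The adaptation sample counts mutation carriers, who may be relatives who tested positive or several members of one family, whereas the RCT randomises index cases. One session is also much less than five modules over up to four weeks with tailored feedback and weekly alerts, so full carry-over is an extreme assumption. The large stated Korean accrual makes heavy chance overlap less likely as well.

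A reader might also infer bias between the arms. Randomisation follows baseline, so pre-exposed families are balanced in expectation and the type I error is unaffected.

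**Conclusion.** The point holds as a permitted and unguarded route to dilution. As written, the plan expressly allows Korean adaptation participants into the RCT and states nothing that keeps Swiss ones out. The sessions show the intervention itself, and neither stratification nor the named primary analysis takes account of it.

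If exposure carries over, the direction is towards no difference. The size is unknown. At an overlap close to what the Korean permission alone allows (10 of 104), power would be about 72-76% instead of 80%; at 20 of 104, about 62-72%. The range runs from full to half carry-over. Overlap, carry-over and the reading of 25% as percentage points are assumptions. The 40-48 carriers are a ceiling, not a forecast.

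**What to change.** State in the RCT eligibility or procedures for both countries (Sample and Sample Size; Recruitment and Procedures, Intervention Efficacy) that a proband is not eligible for the RCT if the proband or a relative attended a session showing intervention modules, mockups or the platform. Qualify the closing sentence of the K-CASCADE consent paragraph to match. Check by family ID before the RCT link is sent. Taking part in the cohort plus either the adaptation or the RCT can remain allowed.

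The cost is one sentence in each place, a lookup, and a somewhat smaller recruitment pool. In Korea the stated accrual of 540 individuals over 3 years is about 270 over the 18-month RCT window (540 × 1.5 / 3), though not all need be probands. In Switzerland, 90 new carriers a year at 50% recruitment give about 67 in 18 months (90 × 1.5 × 0.5), in addition to existing cohort members, whose number the article does not give. If Swiss recruitment proves too tight for exclusion, the minimum is to record prior exposure for each family before randomisation and to add a sensitivity analysis of the primary outcome without those families.
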